As a second aim of the current work, we intend to contribute to filling the gap on the efficacy of ACT as a transdiagnostic approach to adolescents' SAD and GAD and amplify the transdiagnostic application of ACT to adolescents presenting these disorders (Study III). To do so, we will adapt, implement, and investigate the efficacy of an ACT Intervention to adolescents presenting SAD or GAD by exploring:Changes in primary (i.e., anxiety symptoms) and secondary (i.e., flourishing and PI/PF processes) outcomes following intervention. In view of the scarce but promising research on ACT efficacy in adolescents’ SAD [60, 74, 75], and GAD [60], improvements are expected at post-intervention for the two intervention groups (i.e., SAD and GAD), in comparison with a control group.The stability of change over time (i.e., 3 and 6 months after intervention completion). We expect improvements in the two intervention groups to be maintained.The equivalence of the efficacy of the same intervention delivered to the two intervention groups (i.e., SAD and GAD). Even though this aim has not yet been addressed, considering ACT conceptual and therapeutic transdiagnostic premises, similar effects on outcome measures are expected for both clinical groups.Mechanisms of change following the intervention in both intervention groups. Based on research conducted with adults on PI/PF processes as mechanisms of change following ACT [43], we expect similar effects in both intervention groups, with changes in PI/PF predicting changes in primary (i.e., anxiety symptoms) and secondary (i.e., flourishing) outcome variables. Specifically, we expect increases in PF processes and decreases in PI processes to promote lesser anxiety and greater flourishing. Given the lack of research on the role of each PI/PF process in producing changes in anxiety for adolescents’ GAD and SAD and the ACT assumptions that all processes are intertwined in their contribution to human suffering / flourishing [38], there were no grounds to define specific hypothesis regarding the differential role of each PI/PF process in contributing to decreases in anxiety and increases in flourishing between the two samples of adolescents, and so no specific and process-based hypotheses are put forward.

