### Participants recruitment

Participants will be adolescents aged between 14 and 18 years old of both sexes recruited in schools. Informed consent from adolescents and their parents/legal guardians will be required for all potential participants. An initial sample of approximately 400 adolescents from the community will be recruited. All participants will be asked to fill in a set of self-report measures through the *Limesurvey* online platform, and this data will be used for Study I. This set of self-report measures includes the Screen for Child Anxiety Related Disorders (SCARED; [79]) that will be used to screen adolescents to further continue their participation in the study (i.e., Study II and Study III). Specifically, participants scoring higher than one standard deviation above the mean found in a normative sample of adolescents [79] for the Generalized Anxiety or the Social Anxiety subscales of the SCARED (see measures description) will be invited for a clinical structured interview (Mini-Kid; [78],) for the assessment of inclusion/exclusion criteria for the two clinical intervention groups (with SAD or GAD, respectively). Moreover, participants scoring below the mean on the SCARED Reduced Total scale (see measures description) found in the same normative sample [79] will be invited for a clinical structured interview (Mini-Kid [78],) for the assessment of inclusion/exclusion criteria for a group of mentally healthy adolescents. Inclusion criteria for the clinical groups will be presenting a main diagnosis of SAD or GAD, for the SAD and GAD groups, respectively. Inclusion criteria for the mentally healthy adolescents’ sample will be not meeting criteria for a mental health diagnosis. Exclusion criteria for all groups includes presenting cognitive impairment, psychotic symptoms or suicidal ideation, and/or undergoing treatment (e.g., prescribed medication) for a psychiatric condition. Concerning the clinical groups, adolescents presenting both GAD and SAD will be excluded, as its inclusion could confound the study’s results and conclusions concerning the equivalence of ACT for adolescents SAD versus GAD. Adolescents displaying symptoms that warrant attention, but that fall beyond the parameters of this study (e.g., presenting psychotic symptoms, suicidal ideation or both GAD and SAD) will be referred to school psychology services.

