### Sample size

Participants recruited in Study II will be randomly assigned to one of the three groups of Study III (cf. Figure. 1). G*Power was used to calculate sample size considering Study III requirements for repeated measures analysis with two groups (considering that the RCT groups will be compared two at a time) and 4 assessment moments. Power analysis for medium effects (f = 0.25) – chosen based on previous ACT studies with adolescents (e.g., [27–30, 60, 80]) –, with a significance level of 0.05 and power of 0.95 requires a sample size of 25 per group. To account for the expected 17% dropout rate reported in a previous meta-analysis of ACT-based interventions [81], the research team intends to collect 4 additional participants per group. Accordingly, Study II will rely on two clinical groups (i.e., SAD and GAD,n ≥ 87) of at least 44 adolescents each, and a mentally healthy group of 29 adolescents (i.e., total n for Study II ≥ 116). For Study III, the clinical participants (i.e., n ≥ 87) will be then assigned to two intervention groups of 29 adolescents each, one for SAD and one for GAD participants, or to a control group of 29 adolescents, evenly distributed between adolescents presenting with SAD or GAD diagnoses.

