### Data analysis

IBM SPSS Statistics 25 will be used to conduct descriptive analysis. In study I, network analysis will be performed and visualized using R (Version 4.1.3). Network nodes will represent the scores for each PI/PF subscales and total scores for anxiety and flourishing measures. Edges will represent the weight of the correlations between the individual nodes. Centrality metrics (e.g., degree of centrality) will also be computed to investigate how important and influential each node is in the network. In study II, Mplus will be used to investigate the adjustment of a path analysis linking PI/PF processes to anxiety and flourishing, based on overall, comparative and residual based fit-indices. The moderator effect of groups (clinical SAD, clinical GAD and healthy adolescents) in those pathways will be estimated, testing for equality of pathways and means. In Study III, the IBM SPSS Statistics 25 will be used to explore treatment effects using Mixed ANOVAs and considering assessment moments as the within-subject and groups (SAD and GAD receiving intervention and Control Groups) as the between-subject effect; interaction effects will also be considered. Additionally, Mplus will be used to examine mechanisms of change after the intervention by performing two-wave latent change score models. These models allow to explore not only if significant changes emerged across assessment moments, but also to investigate the impact of changes in PI/PF constructs on changes in anxiety or flourishing. All Study III analyses will be carried out according to an intention-to-treat principle as suggested by the CONSORT guidelines [77]. Therefore, all participants randomized will be included in the statistical analyses and analyzed according to the group they were assigned regardless of having received/completed or not the intended intervention. Efforts will be made to obtain outcome data for all participants, even if they do not complete the intervention. If data is missing (e.g., participant refused to provide data, participant was unreachable, etc.) the last observation carried forward method will be employed.

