
Additionally, this project will investigate the efficacy of ACT delivered online via videoconferencing to adolescents with SAD and GAD, compared to a control group. The online delivery of ACT is a relevant strength of this research project. The efficacy of full synchronous online ACT interventions delivered to adolescent SAD and GAD have not yet been investigated. However, this method of delivering interventions may be particularly relevant to adolescents as it is more accessible and it may help to circumvent obstacles to treatment seeking such as autonomy (i.e., being dependent on parents/adults to drive them to clinics), time and money spent on commuting and fear of stigmatization when seeking in-person psychological support [94]. Moreover, adolescents spend more time online than any other age group, and so online interventions have the potential of being a well-received method, thus enhancing the delivery of mental health care within this adolescence [95].

By using a robust RCT design to investigate the efficacy of ACT, this project will address the scarcity of methodologically robust designs examining that topic specifically in relation to mental health conditions in adolescents (e.g., [27–30, 65]). We will also compare the efficacy of the same ACT intervention between GAD and SAD clinical groups, expecting similar effects on outcome measures. Moreover, we will investigate the maintenance of intervention gains over time, which will offer a better understanding of the utility of ACT during a period of significant and rapid physical, psychological, and social changes. If the intervention is found to be efficacious, this project will support the future delivery of ACT interventions to adolescent ADs as a reliable transdiagnostic alternative, and as an added option for those who do not achieve desired results from standard treatments. This may offer clinicians the opportunity to choose interventions based on adolescents needs, while adhering to evidence-based treatments and benefiting from the practical and economical implications of transdiagnostic approaches in clinical practice.

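### Equivalence of ACT in SAD and GAD is a stated aim, but the only named efficacy analysis and sample size are for detecting a difference, and the two arms differ by diagnosis, not by randomisation

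*Protocol article*

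**What the plan says.** Under AIMS, the second aim (Study III) includes "The equivalence of the efficacy of the same intervention delivered to the two intervention groups (i.e., SAD and GAD", with the expectation that "similar effects on outcome measures are expected for both clinical groups". Participants recruitment excludes adolescents with both diagnoses because including them could confound "conclusions concerning the equivalence of ACT for adolescents SAD versus GAD". A conclusion on equivalence is therefore intended, and it shapes eligibility. The Discussion repeats the intention: "We will also compare the efficacy of the same ACT intervention between GAD and SAD clinical groups, expecting similar effects on outcome measures".

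For the analysis, Data analysis says SPSS will be used to "explore treatment effects using Mixed ANOVAs and considering assessment moments as the within-subject and groups" as the between-subject factor, with interactions. The groups are SAD-ACT, GAD-ACT and one Control Group. The sample size rests on a "repeated measures analysis with two groups (considering that the RCT groups will be compared two at a time) and 4 assessment moments". The effect size is given as "Power analysis for medium effects (f = 0.25"), with significance level 0.05 and power 0.95, which leads to 25 per group, raised to 29 for dropout.

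Under Study design and randomization of participants, adolescents are allocated 2:1 to intervention or control within each diagnosis. Controls are assessed twice, 12 weeks apart. The intervention arms are assessed four times. The control group of 29 is to be split evenly between the two diagnoses (Sample size).

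**The concern.** Two things do not fit the aim.

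First, a difference test can reject equality but cannot establish similarity. When the expected result is no difference, a smaller or noisier trial is more likely to produce it. The sample size calculation does not help, because f = 0.25 is an effect to be detected and not a difference to be ruled out.

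Second, what separates SAD-ACT from GAD-ACT is the main diagnosis. The two arms enter through high scores on different SCARED subscales, and their raw changes combine the effect of ACT with whatever would have happened without it. Equal change is equal efficacy only if the untreated courses are also equal. The design randomises controls in both diagnoses, which would allow this to be checked, but the stated analysis treats them as one group.

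At stake is the transdiagnostic claim, the distinctive conclusion of the second aim. It could be supported by imprecision and not by evidence. The randomised comparison of ACT with control is not affected.

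**Working it through.** **Inputs from the article.** 25 per group before dropout, 29 planned; groups compared two at a time; 4 assessments in the ACT arms; f = 0.25; alpha 0.05; power 0.95; about 29/2 = 14.5 controls per diagnosis; intention-to-treat with all randomised participants analysed.

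**Assumptions.** The article gives no correlation between assessments and no margin. I use correlation ρ = 0.5 to 0.7 and, for illustration, a margin of ±0.5 SD. SD is that of the score at one time point.

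**1. Reproducing the plan's figure.** For the group-by-time interaction, λ = f²·N·m/(1−ρ), with df (k−1)(m−1) and (N−k)(m−1). With N = 50, m = 4, k = 2 and ρ = 0.3: λ = 0.0625 × 50 × 4/0.7 = 17.86, df 3 and 144, power 0.952. N = 48 gives 0.944. So 25 per group is reproduced at ρ = 0.3 (at ρ = 0.5 the total would be 36). If two arms differ by a constant D at all three later assessments, f = 0.25 corresponds to D of about 1.15 SD. The trial is thus sized to detect a very large difference between the two ACT arms.

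**2. Precision of SAD-ACT versus GAD-ACT, n = 29 per arm.** SE of the difference in change = √(2(1−ρ)) × √(2/n), with df 56 and t values 2.003 (95%) and 1.673 (90%). P(non-significant) comes from the noncentral t distribution.

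| | ρ = 0.5 | ρ = 0.7 |
|---|---|---|
| SE | 1.000 × 0.263 = 0.263 | 0.775 × 0.263 = 0.203 |
| 95% CI half-width (SD) | 0.53 | 0.41 |
| 90% CI half-width (SD) | 0.44 | 0.34 |
| P(non-significant), true 0.5 SD | 53% | 32% |

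Using all four assessments in the interaction test (N = 58, difference of 0.5 SD sustained) gives nearly the same result: 53% at ρ = 0.5 and 30% at ρ = 0.7. At ρ = 0.3, the value that reproduces the sample size, it is 66%.

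**3. Two one-sided tests at true equality, margin ±0.5 SD.** Equivalence is declared only if the estimate lies within 0.5 minus the 90% half-width.
- ρ = 0.5: within ±(0.5 − 0.44) = ±0.06 SD; power about 19%.
- ρ = 0.7: within ±(0.5 − 0.34) = ±0.16 SD; power about 57%.

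For 80% power at this margin, 69 per arm are needed at ρ = 0.5 on change scores, or 35 per arm with baseline adjustment at ρ = 0.7. Both exceed 29.

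**4. The contrast that addresses efficacy.** This is (SAD-ACT − SAD-control) − (GAD-ACT − GAD-control) at post-intervention. SE = √(2(1−ρ)) × √(2/29 + 2/14.5) = √(2(1−ρ)) × 0.455. With 83 df (t = 1.989), the 95% half-width is about 0.90 SD at ρ = 0.5 and 0.70 SD at ρ = 0.7. The 90% half-widths are about 0.76 and 0.59 SD, both wider than the illustrative margin. Controls have no 3- or 6-month assessment, so the contrast cannot be formed there.

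**The case against.** The strongest reply is that the article never gives the faulty rule. A reader might infer that a non-significant interaction will be declared equivalence. The documents do not say so. The sub-aims are framed as exploration, Data analysis speaks of exploring effects, and the Discussion speaks of comparing. A margin or CI criterion could stand in an analysis plan that is not shown. This stands as a limit on the claim, but it does not remove the mismatch. The article itself sets equivalence as an aim, refers to conclusions on it, names the test and fixes the size. A margin set elsewhere would not change the precision of 29 per arm.

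A reader might also infer that SAD and GAD have different natural courses. The article gives no such data. It describes both as highly stable, and the limitations in the Discussion offer separate SAD and GAD control groups as a contingency if the mixed group proves unsuitable. The supportable point is narrower: similar untreated courses are assumed here and not tested by the stated analysis, although the within-diagnosis randomisation would allow it.

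The figures depend on assumptions. A correlation of 0.7 is clearly kinder than 0.5. Because intention-to-treat keeps all randomised participants, 29 per arm is the right planned number and not a figure reduced for dropout. With baseline adjustment and a correlation of 0.7, power for the assumed 0.5 SD margin rises to 68%, still below 80%. On the other side, carrying the last observation forward can pull both arms' changes towards zero and so towards each other, which is not conservative for equivalence.

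**Conclusion.** The concern holds in this limited form: the article sets an equivalence aim, but its only named efficacy analysis and its only sample size basis are for a difference, in a comparison that is not randomised. Followed as written, the plan cannot support a conclusion of equivalent efficacy. It does not follow that the investigators will equate non-significance with equivalence, only that no other route is given.

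With 29 per arm and an assumed correlation of 0.5 to 0.7, a true 0.5 SD difference would go undetected in about 53% to 32% of trials. The 95% CI would reach about 0.53 to 0.41 SD either side of the estimate, and an equivalence test at an assumed 0.5 SD margin would have about 19% to 57% power. The arm-by-diagnosis contrast is less precise still, at about 0.90 to 0.70 SD either side. Other margins or correlations would change these figures. The mismatch between aim and method does not depend on them.

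**What to change.** - In AIMS and Data analysis, state that a non-significant group-by-time interaction will not be taken as evidence of equivalence.
- Report the SAD-ACT versus GAD-ACT difference on a named common standardised scale with a 90% CI, labelled exploratory. Claim equivalence only if the interval lies wholly inside a margin fixed before analysis. Otherwise report that no difference was shown and equivalence was not established.
- At post-intervention, also report the arm-by-diagnosis contrast against same-diagnosis controls with its CI, as the only contrast that addresses efficacy. State its expected width, and that it cannot be estimated at 3 or 6 months because controls are assessed only twice.

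The cost is a few sentences, with no change to recruitment, assessments or the randomised comparison with control. The downside is that this aim will probably be reported as exploratory or inconclusive.

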## Method

This project is funded by the Portuguese Foundation for Science and Technology (Identifier: 2022.13986.BD) and is registered at ClinicalTrials.gov (Identifier: NCT05906849). All procedures were approved by the Ethics Committee of the Faculty of Psychology and Educational Sciences of the University of Coimbra. Eventual protocol amendments will be communicated to this Committee.

### Study design and randomization of participants

The two aims of this research will be accomplished through diverse study designs. To accomplish the first aim, cross-sectional data will be collected from adolescents within a community sample, two clinical groups (with SAD or GAD), and a mentally healthy sample. For the second aim, a Randomized Controlled Trial (RCT) with a parallel design, 3 groups (i.e., Control Group, SAD Intervention Group, and GAD Intervention Group) and 4 assessment moments will be conducted following the CONSORT (Consolidated Standards of Reporting Trials) guidelines [77]. Adolescents from each clinical group from Study II will be randomly allocated (computer-generated random allocation,2:1 allocation ratio) to one of the intervention groups or to the control group. The two clinical intervention groups will receive the same intervention and will be assessed at pre- and post-intervention, and at 3- and 6- month follow-up using a set of self-report measures (see measures section). Adolescents from the control group will be assessed with the same set of self-report measures at 2 different time points (12 weeks interval), mimicking the pre- and post-intervention assessment moments. Given the high stability of both SAD and GAD, we consider ethical obligations to be imperative in not depriving these adolescents of intervention during follow-up assessments. As such, they will be assessed with a clinical structured interview (Mini-Kid; [78]) after the second time point and referred to the school psychology services if the difficulties persist. A flowchart of the study design is presented in Fig. 1.

**Fig. 1 Fig1:**
[figure not shown]
Flowchart of the design and participants allocation for the three sequential studies

### Participants recruitment

Participants will be adolescents aged between 14 and 18 years old of both sexes recruited in schools. Informed consent from adolescents and their parents/legal guardians will be required for all potential participants. An initial sample of approximately 400 adolescents from the community will be recruited. All participants will be asked to fill in a set of self-report measures through the *Limesurvey* online platform, and this data will be used for Study I. This set of self-report measures includes the Screen for Child Anxiety Related Disorders (SCARED; [79]) that will be used to screen adolescents to further continue their participation in the study (i.e., Study II and Study III). Specifically, participants scoring higher than one standard deviation above the mean found in a normative sample of adolescents [79] for the Generalized Anxiety or the Social Anxiety subscales of the SCARED (see measures description) will be invited for a clinical structured interview (Mini-Kid; [78],) for the assessment of inclusion/exclusion criteria for the two clinical intervention groups (with SAD or GAD, respectively). Moreover, participants scoring below the mean on the SCARED Reduced Total scale (see measures description) found in the same normative sample [79] will be invited for a clinical structured interview (Mini-Kid [78],) for the assessment of inclusion/exclusion criteria for a group of mentally healthy adolescents. Inclusion criteria for the clinical groups will be presenting a main diagnosis of SAD or GAD, for the SAD and GAD groups, respectively. Inclusion criteria for the mentally healthy adolescents’ sample will be not meeting criteria for a mental health diagnosis. Exclusion criteria for all groups includes presenting cognitive impairment, psychotic symptoms or suicidal ideation, and/or undergoing treatment (e.g., prescribed medication) for a psychiatric condition. Concerning the clinical groups, adolescents presenting both GAD and SAD will be excluded, as its inclusion could confound the study’s results and conclusions concerning the equivalence of ACT for adolescents SAD versus GAD. Adolescents displaying symptoms that warrant attention, but that fall beyond the parameters of this study (e.g., presenting psychotic symptoms, suicidal ideation or both GAD and SAD) will be referred to school psychology services.

